#### Assessment protocol 4: community-based care for the frail elderly

The assessment protocol will evaluate three types of specific interventions during the period from 1st January to 31th December 2018: i) Early discharge service (*n* = 144) which includes acute patients admitted to the medical and/or surgical hospital wards and promptly discharged to receive home-based post-acute care and/or rehabilitation; ii) Home-based Case Management service (*n* = 566) which includes complex chronic patients or patients receiving long-term care by a case management nurse; and, iii) Geriatric residences service (*n* = 920) will include patients receiving acute support, post-acute or continued care for elderly people living in geriatric residences. It will be conducted by Badalona Serveis Assistencials (BSA), an IC service provider located in the city of Badalona (216 K inhabitants) in the North-Eastern part of the Barcelona Metropolitan Area.

The current assessment protocol, summarized in Additional file 4: Table S4, aims to assess cost-effectiveness of these three interventions for frail patients, as well as to generate a roadmap for regional scalability of the service. The study protocol will consist of a prospective controlled cohort study wherein each intervention group will be compared with the corresponding usual care group (controls, 1:1 ratio) (*n* = 1630 in each arm), using propensity score matching. Age, sex, GMA, socioeconomic status, number of hospitalisations during the previous year and polypharmacy will be used as matching variables. The patients from the usual care group will be recruited during the study period in the same area. A subset of 250 patients from each control and intervention groups will be thoroughly characterized using a set of standardized questionnaires [26, 27, 30], as depicted in Additional file 4; Table S4.

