(4) Frail elderly patients	(4.1) Assessment of community-based integrated care services for frail patients at BSA	(4.1) Prospective controlled cohort study using PSM methods (2018) (Additional file 4: Table S4)	(4.1) Individuals enrolled in BSA integrated care programs for frail elderly that includes: i) Early Discharge support (*n* = 144); ii) Long-term home-based support services (*n* = 566) and iii) Geriatric residences care (*n* = 920)	(4.1) Individuals living in Badalona receiving usual care: i) After hospital discharge (n = 144), ii) At home (n = 566); and, iii) Living at geriatric residences (*n* = 920)	(4.1a) Cost-effectiveness of the service; and, expanded HDA using MCDA (n = 250). Factors modulating success of the implementation strategy.
					(4.1b) KPI for service assessment

**Abbreviations**: *HDA* Health Delivery Assessment, *MCDA* Multi-Criteria Decision Analysis, *HCB* Hospital Clinic de Barcelona, *PSM* Propensity Score Matching, *KPI* Key Performance Indicators for service long-term assessment after the deployment phase, *BSA* Badalona Serveis Asssistencials

**Table 2 Tab2:** Three main assessment dimensions: effects of the intervention, determinants of success of implementation and maturity of integration

Study Protocol	Outcomes of the intervention [26, 27]		Deployment strategies [28, 29]	Maturity level [4]

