(4) Frail elderly	Health and well-being	Mortality rate, avoidable hospital admissions, total bed days, 30-day readmissions, number of ER visits in the month, physical functioning, psychological well-being, social relationships & participation, enjoyment of life, resilience, autonomy		
	Patient experience	Person centeredness, continuity of care, burden of medication, burden of informal caregiving (Additional file 4: Table S4)		
	Costs	Operational costs		

The current assessment protocols also aim to separately establish key factors that modulate the success of IC service deployments in order to identify their potential for transferability to other sites. To this end, we will use standard implementation science tools [28, 29, 35, 36] to answer the questions delineated in the third column of Table 2, as well as to report the results of the implementation process following standards for reporting implementation studies (StaRI) [28]. This will allow us to identify facilitators, barriers, solutions and critical success factors during the course of the implementation process with relevant implications for analysis of service transferability. It must be highlighted that collaborative tools and methodologies were applied for the implementation of the three service-oriented studies. The process incorporates co-design elements, with participation of different stakeholders, including patients, following a Plan-Do-Study-Act (PDSA) iterative cycles approach [37] adapted to the characteristics of each assessment protocol, as summarized below. Last, but not least, the maturity of the ecosystem in which the service is being deployed will be assessed following the twelve-dimension measurement protocol described in [4] and summarized in the fourth column of Table 2.

It is assumed that the three assessment categories depicted in Fig. 1 and in Table 2: i) Outcomes, ii) Deployment strategies, and, iii) Maturity level, will provide the basis for identification of general, and service-specific, key performance indicators (KPI) useful for long-term follow-up of IC services after the initial deployment period, taking into account outcomes, processes and structure [38].

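### Protocol 4, geriatric residences: controls have no index date and matching ignores any current or recent acute episode, so residents who join the service because of one can be paired with stable residents

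*Protocol article*

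**What the plan says.** The section on Assessment protocol 4 describes the residence service, 920 patients, as one that "will include patients receiving acute support, post-acute or continued care for elderly people living in geriatric residences". The comparator column of Table 1, row 4, gives the control group, also 920, as usual-care individuals in Badalona "iii) Living at geriatric residences". On recruitment of controls the section adds: "The patients from the usual care group will be recruited during the study period in the same area". On matching it says: "Age, sex, GMA, socioeconomic status, number of hospitalisations during the previous year and polypharmacy will be used as matching variables". Each service is compared with its own usual-care group at 1:1.

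The outcomes that Table 2 lists for this protocol begin: "Mortality rate, avoidable hospital admissions, total bed days, 30-day readmissions, number of ER visits in the month".

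Two other comparisons in the article tie the controls to an event. In the same Table 1 cell, the early-discharge controls are "Individuals living in Badalona receiving usual care: i) After hospital discharge (n = 144"). In Assessment protocol 2, the home-hospitalization controls are patients admitted to a ward from the emergency room of the same hospital.

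**The concern.** The service arm is described by the care its members receive, and two of the three kinds of care named imply a present or recent illness episode. The controls are described by where they live. If an episode is what brings some residents into the service, those residents start follow-up at a moment of raised risk, while their matched controls start at no particular moment.

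Several of the listed outcomes cover short windows in which a recent episode would plausibly raise the rate: readmission within 30 days, ER visits in the month, early deaths, and bed days. A service with no effect could then look harmful, and a service with a real benefit could look neutral. The error would carry into the cost-effectiveness aim of Protocol 4 through bed days and admissions. Residences are also the largest of its three comparisons.

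**Working it through.** **1. The plan's own figure.** 144 + 566 + 920 = 1630, which agrees with the stated number per arm. The residence stratum is 920/1630 = 56% of each arm. The article gives no power calculation for this comparison, so there is none to reproduce.

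**2. What the matching list covers.**

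| Feature at entry | In the list? |
|---|---|
| Age, sex, socioeconomic status | Yes |
| Morbidity burden | Yes (GMA) |
| Admissions in the previous year | Yes, as a count |
| Polypharmacy | Yes |
| Time since last admission or discharge | No |
| Current acute episode managed without admission | No |
| Reason for joining the service | No |
| Index date | Not stated |

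The count of previous-year admissions can include the admission that led to a post-acute entry, if the look-back runs up to enrolment. The article does not say whether it does. Even then, one admission ten months ago and one last week count the same, and an episode treated inside the residence does not count at all.

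**3. Size, as an illustration.** Inputs from the article: 920 per arm. Assumed, because not stated: share s of service patients who enter through an episode; factor R by which the episode multiplies the outcome risk after matching; control risk p0 of 10% or 20%; two-sided 5% test; no true service effect; controls not in an episode.

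Service-arm risk = (1 − s)·p0 + s·R·p0, so the apparent risk ratio is 1 + s(R − 1).

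- s = 0.10, R = 1.5: 1 + 0.10 × 0.5 = 1.05
- s = 0.30, R = 2: 1 + 0.30 × 1 = 1.30
- s = 0.50, R = 2: 1 + 0.50 × 1 = 1.50

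Probability of a significant result in the direction of harm (two-proportion normal test, pooled standard error for the critical value, 920 v 920). Without bias it would be 2.5%.

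| s, R | Apparent risk ratio | p0 = 10% | p0 = 20% |
|---|---|---|---|
| 0.10, 1.5 | 1.05 | 10.5% v 10%: 5.4% | 21% v 20%: 7.7% |
| 0.30, 2 | 1.30 | 13% v 10%: 52% | 26% v 20%: 86% |
| 0.50, 2 | 1.50 | 15% v 10%: 90% | 30% v 20%: over 99% |

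If a share c of the controls is also in an episode at the start of follow-up, the ratio becomes [1 + s(R − 1)]/[1 + c(R − 1)]. This is closer to 1 whenever 0 < c < s, and equals 1 when c = s. The table is therefore the case of wholly stable controls.

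**The case against.** The strongest reply is that the sentence on the residence service may describe its scope and not its entry route. Table 1 describes the service arm as people enrolled in the provider's integrated care programmes and names this component simply as care in geriatric residences. On that reading an enrolled resident is compared with a resident under usual care, acute episodes arise in both arms during follow-up, and entry causes no imbalance. The article allows this reading. A reader might infer that the acute episode will in fact be taken for a service effect, but the text does not support so firm a statement. It supports only the conditional one, for whatever fraction enters because of an episode.

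Three further points have weight.

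- It would go too far to say that the matching captures nothing of the triggering event, since the admission count may capture part of it for post-acute entrants. What stays unmatched is recency, and episodes without admission.
- The shares and risk factors above are assumptions. A range that began at a share of 25% would leave out the mild end, where the distortion is small. An excess confined to the weeks after an episode would also fade over a longer follow-up.
- Additional file 4 (Table S4), which is not shown, may define an index event, and an article may leave detailed eligibility to the full protocol.

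The last point does not remove the concern. The article does state a comparator and a matching list, and it ties controls to an event in two other comparisons but not here.

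There is also a warning about the remedy. If residents are enrolled for ongoing care, later episodes are partly outcomes. Choosing controls by an episode that falls after the corresponding enrolment date would condition on an outcome and create a new bias.

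**Conclusion.** The point holds in conditional form. As written, the residence comparison neither aligns the two groups in time nor balances them on a current or recent acute episode. Any resident who joins the service because of one can be matched to a stable resident with a similar year behind them. The likely direction is against the service. The size runs from negligible (apparent risk ratio about 1.05) to large (about 1.5), depending on a share and an excess risk that the article does not give. The upper figure also assumes that no control is in an episode at the start and that the excess persists after matching on GMA and previous admissions. A demonstrated bias of known size is not shown. What is shown is a comparison open to such bias, which can be closed with little effort before analysis.

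**What to change.** In the Assessment protocol 4 section and Table 1, row 4:

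1. State how residents come to be enrolled in the service, and set the index date at enrolment. Give each usual-care control a matched index date.
2. Add to the matching variables the acute-episode status and its recency before the index date: emergency contact, admission or discharge, and acute primary-care contact. State that the look-back for previous-year hospitalisations ends at the index date.
3. Where enrolment was triggered by an acute or post-acute episode, match exactly to usual-care residents at the same kind of episode. For residents enrolled for continued care, match to residents in the same pre-index state.
4. Do not select or exclude anyone, in either arm, on episodes after the index date.
5. Report results by entry type before pooling, with the number in each type.

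If Additional file 4 already fixes an index event for residence controls, bring it into the main text and check it against these items.

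Cost: changes of wording and a registry query. The Methods section says that the regional registry already holds hospital, emergency-room and primary-care data. An episode handled wholly inside the residence with no recorded contact would still be missed. Some matched pairs will be lost in the acute and post-acute strata, so fewer than 920 pairs may remain.

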#### Enhanced risk assessment & service selection

The 2011–2015 Catalan Health Plan extensively implemented a case finding system classifying high risk chronic patients into two different categories based on defined criteria and primary care physician judgement: i) Complex chronic patients (CCP, approximately 3% of the population); and, ii) Patients with less than 12 months expected life survival (Advanced Care Disease, ACD, approximately 1% of the population). The latter category of patients consists of citizens with advanced chronic diseases and/or with oncological problems being potential candidates for palliative care.

Since 2015, the population-based risk stratification tool (i.e. GMA) primarily used for health policy purposes, has been extensively implemented in primary care. The clinical workstation currently displays the GMA grading of the patient being attended by the health professionals, without specific connections with the patient’s care plan. The current assessment protocols offer an opportunity to explore enhanced clinical risk assessment modalities aiming at facilitating preventive strategies, improving service selection and providing clinical decision support. To this end, the assessment protocols will elaborate and evaluate novel approaches to health risk assessment following the orientations described in [39, 40, 42].

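### Protocol 4's case management comparison is at material risk of residual confounding, because the matching list omits the complex-chronic / advanced-disease (CCP/ACD) label

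*Protocol article*

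**What the plan says.** Protocol article, section on Assessment protocol 4: three services are each compared 1:1 with their own usual-care group, 1630 per arm in total. The matching rule is: "Age, sex, GMA, socioeconomic status, number of hospitalisations during the previous year and polypharmacy will be used as matching variables". No CCP/ACD label and no frailty or functional measure is listed.

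The same section describes home-based case management (n = 566) as a service "which includes complex chronic patients or patients receiving long-term care by a case management nurse". On controls it says: "The patients from the usual care group will be recruited during the study period in the same area". Table 1 describes the comparators as "Individuals living in Badalona receiving usual care: i) After hospital discharge", followed by people at home (n = 566) and people in geriatric residences (n = 920).

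The section on enhanced risk assessment and service selection describes a regional case-finding system "classifying high risk chronic patients into two different categories based on defined criteria and primary care physician judgement". The first category is "Complex chronic patients (CCP, approximately 3% of the population"). The second is "Patients with less than 12 months expected life survival (Advanced Care Disease, ACD, approximately 1% of the population").

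Table 2 lists among the Protocol 4 outcomes: "Mortality rate, avoidable hospital admissions, total bed days, 30-day readmissions, number of ER visits in the month".

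**The concern.** Propensity score matching removes confounding only through the variables in the score. In case management, complex chronic status is a stated route into the service, while the controls are described by setting alone. Nearly all of the comparability therefore has to come from the six listed variables.

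The document describes CCP/ACD as a separate classification that carries physician judgement. GMA is described in Methods as resting mostly on statistical criteria. Two people with the same age, GMA grade, admissions and drug count could therefore carry different labels. ACD is defined by short expected survival, so an unequal share of labelled patients would feed into mortality, bed days and admissions, and from there into the cost-effectiveness aim.

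The article's own practice points the same way. Protocol 3 adds clinical variables specific to the service (type of surgery, ASA index) to GMA. Protocol 4 reuses Protocol 2's six variables unchanged. In Protocol 2, however, both arms share an index event, admission from the emergency room of one hospital. No shared event is stated for case management against usual care at home.

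**Working it through.** **1. The plan's own figure.** 144 + 566 + 920 = 1630 per arm, which reproduces. Case management is 566 / 1630 = 35% of the pairs. The article gives no event rate or effect size for Protocol 4, so there is no power calculation to check.

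**2. Where entry differs between the arms**

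| Service | Cases described by | Controls described by |
|---|---|---|
| Early discharge (144) | stay on a hospital ward, then discharge home | hospital discharge |
| Case management (566) | complex chronic status, or nurse-managed long-term care | living at home |
| Residences (920) | living in a residence | living in a residence |

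Only the middle row has a clinical criterion on one side and none on the other.

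**3. How a residual label imbalance would act.** Let p be the share with ACD in an arm after matching, and let m1 and m0 be mortality with and without ACD. With no service effect:

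arm mortality = p·m1 + (1 − p)·m0

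spurious difference = (p_case − p_control) × (m1 − m0)

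The article gives none of these inputs; all of them are assumptions.

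- m1 = 50%, m0 = 10%: a 5-point gap in share gives 0.05 × 0.40 = 0.02, or 2 percentage points (0.02 × 566 ≈ 11 deaths).
- m1 = 30%, m0 = 10%: the same gap gives 0.05 × 0.20 = 1 point.
- m1 = 70%, m0 = 5%: the same gap gives 0.05 × 0.65 = 3.25 points.
- Middle case, m1 = 50%, m0 = 10%, shares 20% vs 10%: cases 0.20 × 0.50 + 0.80 × 0.10 = 18%; controls 0.10 × 0.50 + 0.90 × 0.10 = 14%; difference +4 points, ratio 1.29.
- Shares reversed, 10% vs 20%: −4 points, so the service would look better than it is.
- Equal shares: 0.

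With m1 from 30% to 70%, m0 of 5% or 10%, and shares from 10% vs 5% up to 30% vs 10%, the difference runs from 1 to 13 points.

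**4. Chance of a misleading test in the middle case.** Unpaired comparison, 566 per arm, two-sided 5%: SE = √[(0.18 × 0.82 + 0.14 × 0.86) / 566] = 0.0218; z = 0.04 / 0.0218 = 1.84; probability ≈ Φ(1.84 − 1.96) = 0.45. Over the range in step 3 it runs from about 8% to nearly 100%.

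**5. Supply of labelled controls.** If the regional shares hold in Badalona, 3% × 216,000 = 6,480 people have CCP and 1% × 216,000 = 2,160 have ACD. If all 566 cases were CCP, (6,480 − 566) / 566 ≈ 10 CCP residents would remain per case. This is an upper bound. The article does not say how many of them are in usual care and reachable.

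**The case against.** A reader might infer that CCP/ACD status governs entry to Protocol 4 and that its mortality and bed-day comparison is therefore confounded against the service. The documents do not support that, for five reasons.

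- Complex chronic status is one of two routes joined by an or. ACD is named as an entry route to no service. The article calls ACD patients possible candidates for palliative care, so they may be managed elsewhere and the bias could run the other way.
- The early-discharge and residence controls are described in parallel with their cases. One of those groups is defined by a hospital discharge, not by where people live.
- GMA, prior-year admissions and polypharmacy plausibly overlap with complexity and may balance part or all of the label. The remark about statistical criteria concerns how the tool was built; it does not say that GMA misses complexity.
- Every number in the illustration models ACD, while the label plausibly tied to entry is CCP.
- Additional file 4 is not shown and may state control criteria. No horizon for mortality is given either.

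All of this stands, and it limits the point to a risk in one comparison. It does not remove the risk. The matching list is stated in full, it lacks a judgement-based prognostic label that plausibly corresponds to one route into the service, and the article gives no reason to take balance on that label for granted. Because each service is compared with its own controls, the other two comparisons do not dilute a bias in this one.

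**Conclusion.** The point holds for the home-based case management comparison: 566 pairs, 35% of Protocol 4. There is a material risk of residual confounding. A proven bias, or one of known direction, is not shown. The size is zero if the six variables balance the label. Otherwise it is about 2 mortality points per 5-point residual gap in ACD share, assuming 50% vs 10% mortality, or 1 to 3.25 points over the wider assumed range. For early discharge and residences the documents show no comparable asymmetry; adding the label there is a precaution.

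**What to change.** - **Case management:** add a three-level variable (CCP / ACD / neither), recorded before the index date, to the propensity score. Match exactly on it where enough labelled usual-care controls exist.
- **Early discharge and residences:** add the same variable to the score where it is recorded.
- **All three:** keep the six present variables and report balance on the label after matching.

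The cost is one more variable, which should be obtainable from the primary care records that the study already draws on, and a change of wording in the matching paragraph. Some cases may lose a match. This matters because the Abstract states full coverage of frail chronic patients in Badalona as the aim, so labelled people outside the services may be few or selected. For that reason exact matching should depend on supply and not be required everywhere. Labelling may also vary between practices, so balance on the label does not guarantee balance on the underlying condition.

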### Additional elements toward enhancement of IC services

All four assessment protocols will also integrate the following dimensions described below.

